**Enrolment**												
	Informed consent	X	—	—	—	—	—	—	—	—	—	—
	Eligibility criteria	X	—	—	—	—	—	—	—	—	—	—
	Demographics^b^	X	—	—	—	—	—	—	—	—	—	—
	Medical data^c^	X	—	—	—	—	—	—	—	—	—	—
	Myo-relaxant drugs	X	X	—	—	—	—	—	—	X	—	—
**Assessments**												
	VASp^d^	X	X	—	—	—	—	—	—	X	—	—
	BBT^e^	—	SO	—	—	—	—	—	—	SO	—	—
	MESUPES^f^	—	SO	—	—	—	—	—	—	SO	—	—
	FMA-UE^g^	—	SO	—	—	—	—	—	—	SO	—	—
	mAS^h^	X	SO	—	—	—	—	—	—	SO	—	—
	ABILHAND	—	SO	—	—	—	—	—	—	SO	—	—
	Robotic assessments	—	—	SO	—	—	—	—	—	—	SO	—
	Checklist	—	—	—	—	X	—	(X)^i^	(X)	—	—	—
**Usability**												
	SUS^j^, PSSUQ^k^, TLX^l^, NPS^m^, CSAT^n^	—	—	—	—	—	SO	—	—	—	—	SO
	VAS-smiles^o^	—	—	—	SO	SO	—	SO	SO	—	—	—
**Intervention**												
	Supervised therapy	—	—	—	X	—	—	—	—	—	—	—
	Minimally supervised therapy	—	—	—	—	X	—	(X)	(X)	—	—	—
	Unsupervised therapy	—	—	—	—	—	—	X	X	—	—	—
**Others**												
	Robotic therapy data^p^	—	—	—	PO	PO	—	PO	PO	—	—	—
	Conventional therapy data^q^	—	—	—	X	X	—	X	X	—	—	—
	Adverse events	X	X	X	X	X	X	X	X	X	X	X
	Device deficiencies	—	—	X	X	X	—	X	X	—	X	—

^a^Not applicable.

^b^Demographics include gender, age, year of birth, and hand dominance.

^c^Medical data include stroke onset, lesion type and side, and impaired hand.

^d^VASp: visual analogue scale for pain.

^e^BBT: Box and Blocks Test.

^f^MESUPES: Motor Evaluation Scale for Upper Extremities in Stroke Patients.

^g^FMA-UE: Fugl-Meyer Assessment for upper extremities.

^h^mAS: modified Ashworth Scale.

^i^(X): Performed only for patients who are not ready to train without supervision. These will continue with 5 additional minimally supervised therapy sessions. In this case, the checklist is repeated during the fifth session.

^j^SUS: System Usability Scale.

^k^PSSUQ: Post-Study System Usability Questionnaire.

^l^TLX: raw Task Load Index.

^m^NPS: Net Promoter Score.

^n^CSAT: Customer Satisfaction Score.

^o^VAS-smiles: 5-point visual analogue scale represented by different emoticons used to answer the question “How was your therapy session today?”

^p^Robotic therapy data includes, for example, time of logging in and out, duration of sessions and breaks, number of task repetitions, correct answers, difficulty level of the exercises, and muscle tone data.

^q^Conventional therapy data includes the number and type of standard therapy sessions performed by the patient while participating in the clinical trial.

Before starting the intervention, patients undergo a screening visit with a medical doctor at which the eligibility criteria are checked and demographic and medical data relevant for patient characterization are collected. At the beginning and end of the study, patients undergo a visit with an experienced therapist where clinical assessments are performed to characterize upper limb sensorimotor deficits. Before the first robot-assisted therapy session and at the end of the study, robotic assessments are performed. The baseline robotic assessments are used to tailor the initial difficulty level of the therapy exercises. As robotic therapy is an addition to conventional therapy and this protocol does not comprise a control group, functional recovery is not used to evaluate the efficacy of unsupervised robot-assisted therapy, as it is not possible to infer how much of the recovery is due solely to the addition of robotic therapy, but rather to investigate the possible relation of different impairment profiles on the observed increase in therapy dose.

During the first week of intervention (ie, the supervised phase), a therapist familiarizes the participants with the therapy platform and teaches them how to perform the therapy exercises. During the second week (ie, the minimally supervised phase), participants try to perform the therapy exercises with the device by themselves. A therapist is still present in the room but intervenes only upon request or if deemed to be needed. The first 2 phases consist of 5 sessions of about 45 minutes each, performed on consecutive days (weekends excluded). These sessions are an addition to standard therapy. Therefore, during the study, participants are allowed to fully follow the conventional interdisciplinary rehabilitation program provided by the clinic.

During the last session of the minimally supervised phase, a checklist (Multimedia Appendix 1) is used by the therapist to record whether participants learned how to correctly perform each assigned therapy exercise. The checklist is also used to assess the patient’s functional independence in ambulation and in positioning in front of the device and to decide if the patient meets the requirements to train with the technology in a safe and effective way without supervision. If the requirements are met, the participant can proceed to the unsupervised phase, which lasts for 2 weeks. During the unsupervised phase, patients can independently exercise with the rehabilitation platform during their free time, during dedicated sessions indicated on their therapy schedule, as well as after 5 PM and during the weekend. Specific guidelines on how much to train are not provided. Even though a possible time to train with the device is suggested on the patient’s daily therapy schedule during weekdays, patients are clearly told that they do not necessarily need to attend the session but can rather freely decide when to seek additional therapy within the offered slots or whether to go at all (ie, as a way to simulate home settings).

If, at the end of the first week of minimally supervised therapy, the patients do not meet the requirements to transition to the unsupervised phase, they continue with minimally supervised therapy for an additional week. At the end of the second minimally supervised week, the checklist is performed again. If the patients are now ready for unsupervised training, they can proceed to 1 week of unsupervised therapy; if they are not ready, they undergo a third week of minimally supervised sessions (Figure 2).

During the entire study, the device is placed in an open-access room and an emergency call system is available next to it. Trained personnel of the clinic turn on the device in the morning and turn it off in the evening. If needed, patients are taken to the device by the personnel of the clinic responsible for patient transportation. The personnel might also help patients to position themselves in the correct way in front of the device but do not help with placing the patient’s hand on the handles or operating the device.

The usability of the platform and user experience during robot-assisted therapy is rated a first time at the end of the first week of minimally supervised therapy and a second time at the end of the study. The difference in the ratings between the 2 time points is used to investigate the effect of unsupervised training (ie, of the therapist’s absence) on the perceived usability of the therapy platform and on the user experience during technology-assisted rehabilitation.

Adverse events and device deficiencies are monitored throughout the whole study protocol. The intervention can be discontinued after consultation with medical doctors and therapists or if the participant decides to quit.

For each patient, attendance to the robot-assisted therapy sessions is registered. As attendance to robot-assisted therapy is one of the study outcomes, strategies to increase adherence are not implemented. Reasons for nonattendance are registered a posteriori for each missed supervised or minimally supervised session as well as if patients train for less than 50% of the possible days (ie, less than 7 of 14 days when the patient undergoes 2 weeks of unsupervised therapy or less than 4 of 7 days in cases where the patient undergoes only 1 week of independent training) during the unsupervised phase.

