**Figure 2 figure2:**
[figure not shown]
Design of the interventional study for each of the study participants. All participants undergo a screening visit, baseline assessments, 1 week of supervised therapy, and 1 week of minimally supervised therapy. After the first week of minimally supervised therapy, the therapist checks whether the patient properly learned how to use the technology and is ready for unsupervised training. If yes, the patient proceeds to 2 weeks of unsupervised use. If no, an additional week of minimally supervised therapy is performed. At the end of this second week, the therapist checks again whether the patient can train independently. If yes, the patient proceeds to 1 week of unsupervised therapy. If no, an additional week of minimally supervised therapy is performed. In total, each patient performs 4 weeks of technology-assisted rehabilitation. At the end of the protocol, the clinical and robotic assessments as well as the evaluation of the user experience and usability are repeated for all patients.

**Table 1 table1:** Data collected and procedures (marked with an “X”) performed at each time point of the clinical trial, with primary (PO) and secondary (SO) outcomes indicated. Day 0 corresponds to the first supervised robot-assisted therapy session. The time range indicates how far a procedure can be advanced (–) or postponed (+) for organizational reasons from the precise time point at which it should be performed.

		Screening visit	Baseline clinical assessment	Baseline robotic assessment	Robot-assisted therapy sessions		Usability evaluation 1	Robot-assisted therapy sessions		Final clinical assessment	Final robotic assessment	Usability evaluation 2
Time point		Day –2	Day –1	Day –1	Day 0-6	Day 7-13	Day 13	Day 14-20	Day 21-27	Day 27	Day 27	Day 27
Time range (days)		–4 to +1	±2	±1	—^a^	—	±2	—	—	±2	±2	±2

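### The five usability and experience questionnaires are fixed at Day 13 and Day 27, so for patients who transition late the change read as therapist absence includes a further therapist-present week

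*Protocol article*

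**What the plan says.** Methods, Intervention, has the ratings "rated a first time at the end of the first week of minimally supervised therapy and a second time at the end of the study". Table 1 puts the five questionnaires (SUS, PSSUQ, TLX, NPS, CSAT) at Day 13 and Day 27, each with a window of 2 days either side. The table heading describes the window as "how far a procedure can be advanced (–) or postponed (+) for organizational reasons".

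The same section gives the interpretation: "The difference in the ratings between the 2 time points is used to investigate the effect of unsupervised training". It then equates unsupervised training with the therapist not being there. Primary Outcomes lists this difference among the primary outcomes, although Table 1 tags the questionnaires as secondary. Data Analysis compares the two evaluations by a paired t test or paired Wilcoxon test for each metric and mentions no allowance for when the patient transitioned.

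For patients who do not meet the checklist requirements at the end of the first minimally supervised week, the plan is that "they continue with minimally supervised therapy for an additional week". After that, "If the patients are now ready for unsupervised training, they can proceed to 1 week of unsupervised therapy". Table 1 adapts to these patients in two rows: minimally supervised therapy and the checklist carry a conditional mark in the later weeks, and the footnote adds "In this case, the checklist is repeated during the fifth session". The questionnaire row has no such mark.

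**The concern.** The contrast of interest is therapist present against therapist absent. For a patient who passes the first checklist, Day 13 is the last therapist-present point and everything up to Day 27 is unsupervised. For a delayed patient the last therapist-present point is about Day 20, and none of the five questionnaires is scheduled there. The Day 13 to Day 27 change for this patient therefore adds together a change under minimal supervision and a change under unsupervised use, and the plan names the whole of it after the second.

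The Discussion expects that usability and experience will not fall when patients train alone. If ratings improve over the extra week, part of a real fall after the therapist leaves could be offset. If they worsen over that week, a fall could be reported that belongs to the therapist-present phase. Removing patients who never become unsupervised does not cure this, because delayed patients do transition and stay in the comparison.

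**Working it through.** **Inputs.** Evaluation days 13 and 27, the 2-day window, and the weekly phases (Days 14-20 and 21-27) come from Table 1. The paths come from Methods, Intervention, and the Figure 2 legend. The number of patients comes from Sample Size. The number delayed and the change over the extra week are not given.

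**The plan's own figure.** 10 / (1 - 0.20) = 12.5, rounded up to 13, which agrees with the stated 13. This point disputes no figure.

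**Composition of the interval.** Time between ratings: 27 - 13 = 14 days (Days 14 to 27). Extra minimally supervised week: Days 14 to 20, that is 20 - 14 + 1 = 7 days.

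| Path | Therapist-present days between ratings | Share |
|---|---|---|
| Passes first checklist | 0 of 14 | 0% |
| Passes second checklist (delayed) | 7 of 14 | 50% |
| Never passes, if kept in the test | 14 of 14 | 100% |

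The last row matters because the Figure 2 legend says that "evaluation of the user experience and usability are repeated for all patients". The exclusion of patients who never reach the unsupervised phase is written in the paragraph on therapy content and VAS-smiles, and whether it extends to the questionnaires is unclear. That is a related point and is not needed for this one.

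**Can the window absorb the delay?** Evaluation 1 may fall on Days 13 - 2 = 11 to 13 + 2 = 15. A switch at about Day 20 lies outside it.

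**Effect on the mean.** For a delayed patient with rating R,

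R(27) - R(13) = [R(20) - R(13)] + [R(27) - R(20)].

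The first bracket is therapist-present. If its average among delayed patients is d, and k of the n pairs are delayed, the pooled mean change carries (k/n) x d from it.

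- n = 13, k = 1 to 4 (assumed): 1/13 = 0.08 to 4/13 = 0.31 times d.
- n = 10, k = 1 to 4 (assumed): 0.10 to 0.40 times d.
- k = 0: zero.

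In SUS points, assuming only for scale that d = +10 and n = 13: k = 2 gives 2 x 10 / 13 = 1.5; k = 4 gives 3.1; k = 6 gives 4.6. With d = -10 the signs reverse. None of these values of k or d comes from the documents.

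**After the change.** With the reference rating at about Day 20, a delayed patient's therapist-present share falls from 7/14 to 0/7. On-time patients stay at 0/14.

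**The case against.** Several points on the other side stand in whole or in part.

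- A reader might infer that nothing captures experience at a delayed patient's switch. Table 1 and Data Analysis show otherwise: VAS-smiles is collected at the end of every session in all four weeks and compared across phases. The gap is confined to the five questionnaires.
- A reader might also infer that a failed checklist means the device has not been learned, so that Day 13 is an untrained value. The checklist also covers ambulation and positioning, so a patient may be held back for other reasons. In the minimally supervised phase the therapist steps in only when asked or when needed, so the extra week is not a week of teaching.
- A delayed patient who transitions is still rated once after a minimally supervised week and once after an unsupervised week, and time and practice affect on-time patients as well. This is true, but it does not remove the difference between the groups: only delayed patients have a therapist-present week inside an interval labelled as therapist absence.
- Fixed days keep the interval and prior device exposure equal across patients. This is a real advantage, and moving the reference rating gives it up.
- All 13 patients have completed, so a Day 20 rating can no longer be obtained. This limits the remedy for this study to reporting, and no analysis can recover the missing rating.

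**Conclusion.** The point holds for the five questionnaires. Their timing is the same for everyone, while the transition is not, and the protocol's reading of the difference fits only patients who transition on time. For a delayed patient, half of the interval belongs to the other condition.

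The effect on the pooled result is (k/n) x d. Both k and d are unknown, the direction is unknown, and the effect is zero if nobody was delayed. The stronger reading, that the design biases the result towards finding no drop, is not supported: it needs ratings to improve over the extra week, and nothing in the documents shows that. Nor do the documents show that a drop is more likely in delayed patients. The measures of feasibility and dose, the other primary outcomes, are not touched. The contamination can be removed cheaply from a contrast that the text names as primary, so the change should be made.

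**What to change.** **For the completed patients.** Report the evaluation 1 to evaluation 2 change separately for patients with 2 weeks and with 1 week of unsupervised therapy. Base the statement about therapist absence on the 2-week group. For delayed patients, show VAS-smiles before and after their own switch as supporting evidence. This needs no new data. It leaves fewer patients in the clean comparison.

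**For follow-up use of the approach.** Keep the Day 13 rating for everyone. In delayed patients, repeat the five questionnaires once at the last minimally supervised session (about Day 20), alongside the repeated checklist, and use that last rating as the therapist-present value in the paired comparison. In Table 1 this is one conditional mark in the questionnaire row.

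The burden is one extra set of questionnaires, in delayed patients only, at a session they already attend. The statistical cost is unequal intervals: 27 - 20 = 7 days after three weeks on the device for delayed patients, against 27 - 13 = 14 days after two weeks for on-time patients. Retaining Day 13 lets both versions be reported. With no control group, confounding with time and practice remains for all patients, and the report should say so.

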**Methods:**

Participants of the clinical study are inpatients of a rehabilitation clinic with subacute stroke undergoing a 4-week intervention where they train with a hand rehabilitation robot. The first week of the intervention is supervised by a therapist, who teaches participants how to interact and train with the device. The second week consists of minimally supervised therapy, where the therapist is present but intervenes only if needed as participants exercise with the device. If the participants properly learn how to train with the device, they proceed to the unsupervised phase and train without any supervision during the third and fourth weeks. Throughout the duration of the study, data on feasibility and therapy dose (ie, duration and repetitions) are collected. Usability and user experience are evaluated at the end of the second (ie, minimally supervised) and fourth (ie, unsupervised) weeks, allowing us to investigate the effect of therapist absence.

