### Intervention

This trial is a single-group, interventional clinical study. The study protocol lasts for about 4 weeks for each patient (Figure 2), which is compatible with the duration of an inpatient stay at the rehabilitation clinic and comparable to our previous studies with the RHK [26]. The data collected and procedures performed at each time point are listed in Table 1.

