### Outcome Measures

#### Primary Outcomes

The primary outcomes of this study are the feasibility of the proposed protocol, the dose of unsupervised robot-assisted therapy performed by participants, and the difference between usability and user experience between the phases where a therapist is present (ie, supervised and minimally supervised phases) and the unsupervised phase.

Feasibility is measured as the number of patients who could transition to the unsupervised phase out of the total number of tested patients, attendance during the unsupervised phase, and safety of use. Attendance is defined as the percentage of days out of the total number of offered days where the patient trains with the device at least once, while safety is defined as the number of adverse events and device deficiencies throughout the entire protocol.

The different metrics used to characterize therapy dose are therapy duration in minutes, number of task repetitions (ie, the number of target movements performed), and percentage change in physical therapy time with respect to the conventional therapy program. Total conventional physical therapy time is estimated from the sum of the duration in minutes of the physiotherapy (without differentiating between upper limb and lower limb) and occupational therapy sessions regularly performed by each patient at the clinic.

Platform usability is assessed with the System Usability Scale [29], the raw Task Load Index [30], and the Post-Study System Usability Questionnaire [31]. User experience during robot-assisted therapy is assessed with the Net Promoter Score [32] and the Customer Satisfaction Score, as well as by evaluating the reasons (if any) for not attending the therapy sessions with the device.

The results of the checklist used to define which patient can proceed to unsupervised therapy are also used to identify specific aspects of the platform that might need to be further improved.

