### Data Analysis

Descriptive statistics will be used to describe the study population (eg, demographics, initial clinical scores, and changes in clinical scores, such as functional recovery), attendance and therapy dose in the unsupervised phase, user experience, and platform usability.

Normal distribution of the data will be checked with the Shapiro Wilk test. For each usability metric, a paired *t* test (normal distribution) or a paired samples Wilcoxon test (for data not normally distributed) will be performed to compare the data collected during the usability evaluation 1 and usability evaluation 2 sessions.

To evaluate the content of unsupervised therapy, 1-way repeated measures ANOVA or its nonparametric version (Friedman test) with post hoc tests will be run to compare intensity (average block intensity for each patient), performance, and ratio of effective therapy time to total session duration during supervised, minimally supervised, and unsupervised therapy. The same tests will be used to compare the answers to the VAS-smiles, a 5-point VAS represented by different emoticons, performed at the end of each therapy session during the 3 phases. For these comparisons, we expect therapy content and VAS-smiles not to vary significantly depending on the level of supervision, as ideally the absence of the therapist should not impact these outcomes. Patients who did not reach the unsupervised phase will be excluded from this analysis.

Linear mixed-effects models will be used to investigate parameters (eg, demographics and baseline data) possibly influencing the achieved dose of unsupervised therapy.

Relevant qualitative data will be summarized and reported accordingly.

Data analysis will be performed with MATLAB R2021b (MathWorks).

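### Changes between phases are read as the effect of the therapist's absence, but with one group and a fixed phase order they also contain practice, recovery and elapsed time

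*Protocol article*

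**What the plan says.** The design is stated plainly in Methods, Intervention: "This trial is a single-group, interventional clinical study". The Figure 2 caption fixes the start of the sequence: "All participants undergo a screening visit, baseline assessments, 1 week of supervised therapy, and 1 week of minimally supervised therapy". Unsupervised use comes after that, and only for patients who pass the therapist's checklist.

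Usability and user experience are rated on day 13 and day 27 (Table 1). Methods, Intervention interprets the contrast: "The difference in the ratings between the 2 time points is used to investigate the effect of unsupervised training", which it explains in brackets as the effect of the therapist's absence. The Abstract (Methods) describes the two ratings as "allowing us to investigate the effect of therapist absence". Primary Outcomes includes "the difference between usability and user experience between the phases where a therapist is present (ie, supervised and minimally supervised phases) and the unsupervised phase".

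Secondary Outcomes uses differences in intensity and task performance to judge whether therapy content varies once the therapist has gone, with the effective-time ratio as a third metric. Data Analysis compares "intensity (average block intensity for each patient), performance, and ratio of effective therapy time to total session duration" across the three phases by one-way repeated measures ANOVA or Friedman test, and VAS-smiles likewise. It expects no significant variation with level of supervision.

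On functional recovery, the Intervention section is cautious. Robotic therapy is added to conventional therapy and there is no control group, so "it is not possible to infer how much of the recovery is due solely to the addition of robotic therapy".

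**The concern.** The caution applied to functional recovery applies equally to the phase contrasts, but the article does not extend it to them. Its only caveat of this kind, in the Discussion, is that the clinical setting may influence adherence and dose.

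Between the two ratings, patients who entered within 6 weeks of stroke onset go on recovering, follow the full conventional programme, gain practice on the robot and meet exercises whose difficulty adapts to their performance. All of this happens while supervision is withdrawn.

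Two wrong conclusions are possible. A practice or recovery trend could be reported as an effect of the therapist's absence. A real loss when the therapist leaves could be offset by improvement and reported as no effect. The second matters more here, because the result hoped for is that usability does not drop (Discussion) and that content and VAS-smiles do not vary (Data Analysis). An offset loss would look like success.

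**Working it through.** **Inputs from the article.** One group; fixed order; ratings on days 13 and 27; 13 patients, from 10 plus about 20% dropout (Sample Size); paired t or Wilcoxon for the ratings; repeated measures ANOVA or Friedman for content and VAS-smiles. No SD, effect size or significance level is given. Two-sided 0.05 and the shifts below are assumptions.

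**1. Sample size.** 10 / (1 − 0.20) = 12.5, rounded up to 13. The plan's figure reproduces, so n = 10 and n = 13 are used.

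**2. What the rating difference estimates.** Let T be the effect of two more weeks (practice, recovery, other therapy) and A the effect of the therapist's absence. For a patient who transitions on schedule:

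- rating 1 = a
- rating 2 = a + T + A
- expected difference = T + A

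With columns for intercept, evaluation 2 and unsupervised, the only rows are (1,0,0) and (1,1,1). The rank is 2 of 3, so A cannot be estimated separately.

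For content on the standard schedule, the minimally supervised indicator equals the week 2 indicator, and the unsupervised indicator equals week 3 plus week 4. Intercept, three week indicators and two phase indicators have rank 4 of 6.

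**3. Spurious effect in the ratings (A = 0).** With d = T / SD of the paired difference, the noncentrality is d√n and

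P(reject) = 1 − F(t_crit) + F(−t_crit), where F is the noncentral t distribution function on n − 1 df.

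At d = 0.5:
- n = 13: t_crit = 2.179, noncentrality 0.5 × √13 = 1.803, P = 0.38
- n = 10: t_crit = 2.262, noncentrality 0.5 × √10 = 1.581, P = 0.29

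| Assumed d | n = 13 | n = 10 |
|---|---|---|
| 0.3 | 0.17 | 0.14 |
| 0.5 | 0.38 | 0.29 |
| 0.8 | 0.75 | 0.62 |
| 1.0 | 0.91 | 0.80 |

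The nominal value is 0.05.

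**4. Masked effect.** With T = +0.5 SD and A = −0.5 SD, T + A = 0 and the test rejects 5% of the time. Even with no time trend, the 95% interval half-width is t_crit/√n: 0.60 SD at n = 13 and 0.72 SD at n = 10.

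**5. Session-level metrics.** Assume 10 patients; 5, 5 and 10 sessions in the three phases; session SD 0.7; a linear practice trend; A = 0.

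- The mean session number is 8 in the minimally supervised phase and 15.5 in the unsupervised phase, a gap of 7.5.
- The SD of the difference in phase means is 0.7 × √(1/5 + 1/10) = 0.383.
- Slope 0.02: difference 0.15, d = 0.39, P = 0.20.
- Slope 0.05: difference 0.375, d = 0.98, P = 0.79.
- Slope 0.05 with a true drop of 0.375 at transition: difference 0, P = 0.05.

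In simulation, a per-patient straight line with a step at transition, with a t test on the steps, rejected about 5% of the time when there was no step. It detected the 0.375 drop in 38% of trials.

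**The case against.** Patients have to learn an active robot before they use it alone, so the fixed order may be unavoidable. This is a small feasibility study meant to inform a larger one, and a before/after change legitimately answers the practical question of whether ratings hold up in unsupervised use. That stands. The objection is to the causal wording, not to the design or to reporting the difference.

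A reader might infer that time and absence are completely inseparable. The documents do not support that. Some patients transition a week late or never, and all repeat the ratings. An illustrative split of 11 patients on schedule and 2 off it raises the ranks to 3 of 3 for the ratings (2 never transitioning) and 5 of 6 for content (2 transitioning late). These patients do not rescue the attribution, however. They are few and selected by failing the checklist, and no such contrast is planned. Those who never transition are excluded from the content and VAS-smiles analysis.

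A reader might also infer that the repeated measures ANOVA is invalid and must be replaced by a step model. That goes too far:

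- Under step 5 the omnibus test rejects more often (36% and 99%), but it includes the supervised week and so does not measure the therapist's withdrawal. In the masking scenario it rejects about 45% of the time for that same reason. Adding patient-by-phase variation lowers the 36% and 99%.
- A mixed model with only a random patient intercept has its own error. With patient-by-phase SD of 0.3 to 0.5 and no mean step, its false-positive rate was about 10% to 17% in simulation.
- An unbounded linear trend suits the metrics poorly. VAS-smiles has 5 points, and 0.05 per session over 20 sessions is a full point. The effective-time ratio cannot exceed 1.

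Finally, no trend model can help the questionnaires, which have only two time points.

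**Conclusion.** The concern holds as one of interpretation. The article explicitly equates the day 13 to day 27 change, a primary outcome, with the therapist's absence, and reads phase differences in content and VAS-smiles the same way. In patients on the standard schedule the rating difference estimates time plus absence, and the planned tests have no term that separates them.

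The identifiability argument needs no assumed figures. The size of the error does: a time shift of 0.3 to 1.0 SD of the paired difference gives a spurious rejection probability of 0.17 to 0.91 at n = 13 and 0.14 to 0.80 at n = 10. These are illustrations, since the article gives no SD. The masking result means that the expected finding of no change cannot show that absence is harmless.

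The documents do not support the stronger conclusions that the design is faulty or that the phase comparison must be abandoned.

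**What to change.** **Wording.** In the Abstract (Methods), Intervention, Secondary Outcomes and Data Analysis, describe the results as change from day 13 to day 27, or between consecutive phases, combining unsupervised use, practice and recovery. Name concurrent conventional therapy, adaptive difficulty and elapsed time as further explanations. Drop the attribution to therapist absence, and state that a non-significant difference does not show that absence has no effect.

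**Supportive analysis for metrics logged every session** (intensity, performance, effective-time ratio, VAS-smiles). Keep the planned phase comparison. Add session-level plots and a per-patient trend-plus-step estimate at the patient's own transition, or a mixed model with random step and random slope. Report the estimate with its interval.

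**Cost.** Rewording and modest programming. The session data are already collected, and the article says analysis was still ongoing. The downside is that the step estimate is imprecise with 10 to 13 patients and assumes a roughly linear practice trend. For the questionnaires, rewording is the only remedy.
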